## Abstract

**Background:**

Given the paucity of current safety studies related to e-cigarettes, there are no definitive studies on whether e-cigarettes cause oral mucosal lesions or even oral cancer. Although it is still undetermined whether e-cigarettes are harmless, an increasing number of teenagers choose to smoke e-cigarettes and believe that they are not harmful to the human body.

**Objective:**

This aims to determine whether e-cigarettes cause damage to the oral mucosa. This study also aims to evaluate the association between e-cigarette smoking and oral mucous membrane lesions in young adults. The objectives are to (1) compare the oral mucosal conditions in participants with and without e-cigarette smoking habits, (2) assess the effect of the amount of e-cigarette smoking on oral mucosal conditions, and (3) assess the effect of the duration of e-cigarette smoking on oral mucosal conditions.

**Methods:**

In this prospective study, 304 youths aged 15 to 24 years (n=152, 50% who smoke only e-cigarettes and n=152, 50% who do not smoke e-cigarettes or cigarettes) will be divided into 2 groups for a controlled study. Whether e-cigarettes cause oral mucosal lesions will be verified by comparing the odds of oral mucosal lesions in the 2 experimental groups. For this experiment, the predefined power is 80% (*P*=.04), and the predefined proportions of groups 1 and 2 are 11% and 2.5%, respectively.

**Results:**

This experiment is at the conceptualization phase and has not yet been carried out. Experimenters have not been recruited and no data have been collected.

**Conclusions:**

e-Cigarettes are still an unfamiliar topic to the public, and it is still unknown whether they can cause damage to the oral mucosa. This experiment aims to find out whether there is a link between the 2. There are still many limitations in this study, such as the lack of categorization of e-cigarettes and the lack of testing methods for oral mucosal status. These limitations are expected to be addressed in the future as the experiment is formally conducted and further optimized.

**International Registered Report Identifier (IRRID):**

PRR1-10.2196/53644

## Introduction

### Background

Oral cavity cancer is the most prevalent head and neck malignancy worldwide [1,2]. This malignant phenotype is often associated with habitual and lifestyle factors, such as tobacco smoking, excessive alcohol consumption, betel nut chewing, and low intake of fruits and vegetables [1]. Due to restrictive government policies and proven negative health effects in many parts of the world, the use of tobacco has declined in recent decades [3]. Electronic cigarettes (e-cigarettes) were invented by a Chinese pharmacist, Hon Lik, in 2003, who envisioned that they would replace conventional cigarettes due to their deleterious effects [4]. e-Cigarette companies claim that handheld devices can provide smokers with the same experience as conventional cigarettes while reducing their negative effects. e-Cigarettes were introduced with the hope that the smoking population would gradually stop using conventional cigarettes and switch to e-cigarettes. With the waning consumption of regular cigarettes, the use of e-cigarettes has surged worldwide, indicating that smokers now consider e-cigarettes viable replacements. Moreover, recent data have indicated that e-cigarette smoking practices are more common among teenagers and young adults [5,6]. However, most people do not take this soaring statistic seriously and allow young people to use e-cigarettes freely. Most people believe that the health hazards of smoking only manifest with increasing age and, thus, concern is unnecessary regarding the use of e-cigarettes by young people.

It is no surprise that young adults are the primary habitual e-cigarette users. The portability of the devices, different flavors with less nicotine, and convenient use of e-cigarettes make them appealing to young people. Data from the 2011-2018 National Youth Tobacco Survey in the United States demonstrated that e-cigarette use among high school students increased from 1.5% in 2011 to 20.8% in 2018 [3]. In 2022, the Centers for Disease Control and Prevention indicated that 2.55 million US middle and high school students reported current (past 30 days) e-cigarette use; nearly 85% of these young people used flavored e-cigarettes, and more than half used disposable e-cigarettes [7]. This increase has also become noticeable in community settings. Unfortunately, adults do not pay enough attention to the use of e-cigarettes, especially in schools.

Current research on e-cigarettes has solely focused on their ingredients and compared satisfaction levels of e-cigarettes with those of regular cigarettes [8,9]. The safety of e-cigarettes, especially regarding the etiology of oral and maxillofacial diseases or other possible intraoral side effects, is still unclear. Moreover, few studies have reported on the adverse effects of e-cigarette smoking [10]. Recent experiments have only indicated that the use of e-cigarettes could impact the balance in the oral microbiome while allowing for the rapid growth of foreign microorganisms [4]. Nevertheless, many studies recommend that individuals replace cigarettes with e-cigarettes irrespective of concerns about their safety.

Smoking causes damage to the oral mucosa as well as lesions that can lead to the progressive development of oral cancer [11]. According to research, smoking can cause “oral mucosal leukoplakia” and a variety of other oral mucosal diseases. Additionally, it has been shown that leukoplakia is the oral mucosal lesion that is most likely to lead to oral cancer [12]. Most of the white spots on the lips occur on the lower lip, in the junction of the middle, and on the outer third of the lip, which is where people usually hold cigarettes; this can explain the relationship between holding cigarettes and white spots on the lip. White spots are precancerous lesions, and approximately 4% to 7% can develop into oral cancer. According to statistics, 93.1% of patients with oral white spots are smokers [13]. The development of oral mucosal lesions is based on the principle that tobacco irritates the oral mucosa (through cigarette smoke and the chemicals in cigarettes), causing it to react adversely to prolonged irritation. e-Cigarettes operate in a similar way to tobacco, which also irritates the oral mucosa through atomization and chemicals.

The only difference between e-cigarettes and cigarettes is simply that e-cigarettes do not contain tar; both contain many chemicals as well as nicotine. e-Cigarettes tend to have more types of chemicals than cigarettes because of the wide variety of flavors.

Given that it is still unknown whether e-cigarettes influence the development of oral mucosal lesions, the possibility that e-cigarettes can cause damage to the oral mucosa and increase the risk of oral cancer similar to tobacco needs to be studied.

To date, no definite investigation of the association between e-cigarettes and oral cavity cancer has been conducted. When available, this study will be the first to determine whether e-cigarettes are mechanistically linked to the development of oral cancer to further educate young users and students on the potential for malignancy due to e-cigarette use. It is assumed that e-cigarettes cause damage to the oral mucosa and oral cancer, which is similar to cigarettes. The following experimental studies and designs will be conducted to test this hypothesis. Therefore, this study aims to investigate the association between e-cigarette smoking and oral mucosal health status among young adults and determine whether e-cigarettes cause damage to the oral mucosa and increase the risk of oral cancer. Compared to that of other similar studies, the methodology of this study is simpler, and the results will be clearly comparable. If the results show that e-cigarettes can cause damage to the oral mucosa similar to that caused by cigarettes, this study could provide strong support for subsequent experiments to determine whether e-cigarettes cause oral cancer.

### Hypothesis

This study hypothesizes that e-cigarettes, in the speculated absence of tobacco, may still induce carcinogenesis. Alternatively, it is suggested that this habit may trigger an imbalance in the oral microbiome that predisposes the mucosal epithelium to oral cavity cancer with other etiological factors. This presupposed risk is likely proportional to the frequency and duration of e-cigarette smoking. The oral mucosal health of participants will be determined by determining the presence of white spots in the mouth (the main feature of the oral mucosa that is damaged by smoking behavior).

### Primary Outcome

The primary outcome is the effect of e-cigarette smoking on oral mucosal conditions.

### Research Significance

The results of this study will provide preliminary evidence of the malignant potential of e-cigarettes in the deterioration of oral mucosal conditions or exclude them as a cause of oral carcinogenesis. If a direct association is observed, the results of this study would be vital to inform e-cigarette users of the harmful and even carcinogenic nature of e-cigarette smoking, despite e-cigarettes being considered tobacco free. In addition, this would help guide the implementation of legislative policies to bring awareness to the additional risks associated with the use of e-cigarettes and vaporizers. Moreover, these findings, if positive, will pave the way for future research on chemical products that may be present in e-cigarettes that are directly involved in the malignant transformation of oral keratinocytes.

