### Sampling Methods

Convenience and nonprobability sampling methods will be used for the recruitment of cases and controls. The detailed sample size determination is shown in Multimedia Appendix 1 [16]. Briefly, the predefined power is 80% (*P*=.04), and the predefined proportions of the case and controlled groups are 11% and 2.5%, respectively. In all, 304 youths aged 15 to 24 years (n=152, 50% who smoke only e-cigarettes and n=152, 50% who do not smoke e-cigarettes or cigarettes) will be recruited.

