### Data Collection: Questionnaire

Interviewer-administered questionnaires will be used to collect data on demographic, lifestyle, and socioeconomic variables for the cases and controls. The questionnaire tool will comprise 2 parts: exposure information (part A) and sociodemographic information (part B). A life grid sheet will be used during interviews to efficiently collect retrospective information on lifestyle habits and other risk factors. To reduce observer bias, interviewers will not initially be informed about the aim of the research. Once cases are identified and interviewed, matching controls will be recruited and interviewed. Answers provided by participants will be converted to objective scores after data collection by the investigator (SC). The details on the parts of the questionnaire are as follows.

Exposure information (part A) will include (1) oral mucosal health status (whether white spots are present), (2) smoking habits, (3) type of products used, (4) e-cigarette smoking status (yes or no and current or previous), (5) age of onset, (6) duration of smoking, (7) pattern of smoking duration (continuous or intermittent), (8) frequency of smoking (daily, weekly, and occasionally), (9) number of cartridges (frequency), and (10) Tobacco consumption. Sociodemographic information (part B) will include (1) age, (2) sex, (3) occupation type, (4) education level, (5) income, and (6) ethnicity.

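### The article says its results may rule e-cigarettes out as a cause of oral cancer, but the only outcome named is white spots, and even for white spots a null result could leave a large increase in odds open

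*Protocol article*

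**What the plan says.** **Claims about cancer.** Research Significance describes two possible readings of the results: preliminary evidence of malignant potential, or results that "exclude them as a cause of oral carcinogenesis". It adds that a direct association would be vital for telling users that e-cigarettes are harmful and even carcinogenic. The Background says the study will be the first to "determine whether e-cigarettes are mechanistically linked to the development of oral cancer", and it gives as an aim finding out whether e-cigarettes raise the risk of oral cancer.

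**What is measured.** The Primary Outcome section reads: "The primary outcome is the effect of e-cigarette smoking on oral mucosal conditions". The Hypothesis section says mucosal health will be judged by "determining the presence of white spots in the mouth". In Data Collection: Questionnaire the item is "oral mucosal health status (whether white spots are present". The three numbered objectives in the Abstract also concern oral mucosal conditions only.

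**More modest text.** The Background also says that a positive finding would support later experiments on whether e-cigarettes cause oral cancer.

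**Size and analysis.** Sampling Methods gives 304 people, 152 per group, 80% power with P = .04, and "the predefined proportions of the case and controlled groups are 11% and 2.5%, respectively". Data Analysis plans odds ratios with 95% CIs and uses P < .05. It gives no equivalence margin or other criterion for concluding that there is no effect.

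**The concern.** The stated conclusions go beyond the data in two steps. The first is from white spots to cancer: the study collects nothing on cancer, so it cannot show or rule out a cause of it. The second is from a non-significant result to absence of effect: the study is sized for a very large difference, so failing to find it says little about smaller but important harm.

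The Abstract notes that growing numbers of teenagers already believe e-cigarettes are harmless. A null result presented as ruling out a cause of cancer would be false reassurance to that group. A positive result presented as evidence of carcinogenicity would be over-read, and Research Significance expects it to guide legislation.

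**Working it through.** **Step 1. Claim against measurement.**

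| Claim | Where | Data item that could support it |
|---|---|---|
| Rule out a cause of oral cancer | Research Significance | None |
| Show carcinogenic nature to users | Research Significance | None |
| Settle a mechanistic link to oral cancer | Background | None |
| Raised risk of oral cancer | Background | None |
| Effect on oral mucosal conditions | Primary Outcome, Objective | White spots, yes or no |

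In the Methods, oral cancer appears only in the exclusion criteria. Participants are aged 15 to 24, and the use required for entry is about 7 months. The Hypothesis section also proposes a second route to cancer, through the oral microbiome, and the questionnaire has no microbiome item. Even a very precise null on white spots would leave that route untested.

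**Step 2. Reproduce the plan's power.** Inputs from Sampling Methods: 152 per group, 0.11 v 0.025, P = .04, taken here as two-sided because sidedness is not stated.

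- Mean proportion 0.0675; difference 0.085.
- SE under the null: √(2 × 0.0675 × 0.9325 / 152) = 0.02878.
- SE under the alternative: √((0.11 × 0.89 + 0.025 × 0.975) / 152) = 0.02836.
- z = (0.085 − 2.054 × 0.02878) / 0.02836 = 0.91, so power is 81.9%. This is close to the stated 80%.
- Design odds ratio: (0.11/0.89) / (0.025/0.975) = 4.82.

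**Step 3. What a null on white spots would leave open.** At 2.5%, 152 × 0.025 = 3.8 lesions per group, so take 4 v 4. The Woolf 95% CI for an odds ratio of 1.0 with *a* lesions in each group is exp(±1.96 × √(2/a + 2/(152 − a))).

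| Lesions per group | Rate | SE of log odds ratio | 95% CI |
|---|---|---|---|
| 4 v 4 | 2.6% | √(2/4 + 2/148) = 0.717 | 0.25 to 4.07 |
| 10 v 10 | 6.6% | √(2/10 + 2/142) = 0.463 | 0.40 to 2.48 |
| 17 v 17 | 11.2% | √(2/17 + 2/135) = 0.364 | 0.49 to 2.04 |

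Non-significant results that lean towards harm leave more open: 6 v 4 gives 1.52 (0.42 to 5.50), and 10 v 4 gives 2.61 (0.80 to 8.50). If both true rates are 2.5%, the upper limit reaches 4 in about 58% of non-significant results.

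**Step 4. Power for smaller effects.** Control rate 2.5%, 152 per group, two-sided .05.

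| True odds ratio | E-cigarette rate | Power, exact for the chi-square test | Power, normal approximation |
|---|---|---|---|
| 2 | 4.9% | 18.5% | 19.4% |
| 3 | 7.1% | 47.9% | 47.2% |

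Real harm of either size would be missed more often than found.

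**The case against.** The best defence is that the sentence is rationale in the Introduction and not an analysis rule. The formal objectives and the primary outcome concern the mucosa only, one half of the Research Significance sentence is hedged as preliminary, and the Background defers the cancer question to later work. Data Analysis already plans the odds ratio with its 95% CI. The Background also describes white spots as precancerous, so the outcome is not irrelevant to cancer.

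Much of this is fair, and it narrows the point. The hedge, however, covers only the positive half; the ruling-out half is unqualified. The modest passages show that the article is inconsistent, and they do not withdraw the stronger claims. A precursor lesion can motivate later work, but it does not replace a cancer outcome. The planned interval helps with reading a null on white spots and does nothing for the inference to cancer.

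Four stronger readings are tempting, and the article does not support them:

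- *A non-significant test must be reported as showing no cancer effect.* Data Analysis contains no such rule. The problem lies in the stated significance and aims.
- *Any null result would be compatible with a fourfold increase in odds.* That depends on a lesion rate near 2.5%. With more lesions the upper limit falls, as step 3 shows.
- *Expected cancers can be counted from the Background's 4% to 7% progression figure.* That figure has no time horizon or age group and stands in a discussion of tobacco smoking. The count would also be beside the point, since no cancers are ascertained.
- *The Hypothesis wording, "may still induce carcinogenesis", is itself an overclaim.* It is a hedged hypothesis and says nothing about what the results will show.

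Study Design speaks of following participants and observing lesions develop, while the questionnaire holds a single yes/no item. Whichever applies, no cancer outcome is added.

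**Conclusion.** The point holds. On the outcomes named, no result of this study can rule e-cigarettes in or out as a cause of oral cancer, and the article conflicts with itself by claiming this in two places while deferring it in another. This part needs no numerical assumption.

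For white spots, the design detects an odds ratio near 4.8 and has about 18% power at 2 and 48% at 3. Equal observed counts leave an upper limit of about 4.1 at the article's 2.5% rate, 2.5 at 10 v 10 and 2.0 at 17 v 17. So even at about 11% in both groups, a doubling of the odds stays within the interval. These figures assume 152 analysed per group, an unadjusted comparison and two-sided tests, and the power figures assume a 2.5% control rate. The detailed sample size appendix is not shown, and nothing here counts against it.

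**What to change.** 1. In Research Significance, delete the clause on ruling out a cause of oral cancer and the statement that an association would show e-cigarettes to be carcinogenic.
2. In the Background, delete the claim to settle a mechanistic link to oral cancer and the aim of showing a raised cancer risk. Keep the sentence that leaves cancer to later experiments.
3. Add wording such as: *This study estimates the association between e-cigarette use and the presence of oral white spots. A non-significant result will be interpreted from the odds ratio and its 95% CI and will not be taken as absence of effect. No inference about oral cancer will be drawn from either a positive or a null result.* The phrase on malignant potential should be brought into line with this.

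No sample size, data item or test changes, because the odds ratio and interval are already planned. The article reports that no data have been collected and that neither registration nor ethics review has been sought, so the wording can be settled before either. The cost is a more modest statement of what the study can show.

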## Methods

### Trial Registration

Given that this study is at this stage of conceptualization and has received no support or sponsorship from any organization at this time, this experiment has not yet been applied for trial registration. The registration will be done in the future when support is received from the relevant organizations.

### Ethical Considerations

This study has not yet been submitted to the ethical review board for assessment, mainly due to lack of financial support and lack of assistance from large organizations. We emphasize that this is an independent study and is still at the research protocol stage. As the project has not received sufficient financial support, we are unable to cover the costs of applying for evaluation by the ethics review committee at this time. At this stage, we are working to ensure that the study design meets ethical standards and will seek possible review and approval at a future stage. We understand and value participant rights and will take appropriate measures to ensure the ethical and legal nature of the study.

### Study Design

The adoption of a case-control, prospective, observational study design is motivated by the relatively low incidence of oral mucosal lesions within the general population. This design allows for a focused exploration of the relationship between e-cigarette smoking and oral mucosal health.

Case-control design is particularly suitable for investigating rare outcomes such as oral mucosal lesions, as it efficiently compares individuals with the outcome of interest (cases) to those without (controls).

A prospective design involves following participants over time, allowing for the collection of data on exposures and outcomes as they occur. By prospectively tracking participants, the study can gather real-time information on e-cigarette smoking habits and observe the development of oral mucosal lesions, providing a temporal sequence crucial for establishing causation.

An observational design is chosen over an experimental one due to ethical considerations and the nature of the research question. Since randomly assigning participants to smoke e-cigarettes for an extended period is ethically challenging, an observational approach allows for the examination of naturally occurring exposure to e-cigarette smoking in real-world settings.

The low incidence of oral mucosal lesions in the general population necessitates a design that efficiently targets and investigates this specific outcome. By focusing on a population at risk (e-cigarette smokers) and carefully selecting controls, the study maximizes its ability to detect and understand the potential impact of e-cigarette smoking on oral mucosal health.

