## Discussion

In examining the potential negative impact of e-cigarettes on the oral mucosa, this study deliberately focused its investigation on this specific aspect, excluding other potential confounding factors that might influence the results. Notably, variables such as alcohol consumption, daily routines, and gender differences were not considered in the experimental design. While these factors were omitted from this study, they were duly documented in the questionnaire phase, laying the groundwork for future investigations to delve into these variables. This strategic choice aimed to isolate the primary relationship between e-cigarette use and oral mucosal health, with the intention to refine and expand the scope in subsequent research endeavors.

The findings of this study align with existing literature on e-cigarettes, which suggests a correlation between the chemicals present in e-cigarettes and cytotoxicity, leading to damage to the oral mucosa. This corroborates with prior research, providing further evidence of the potential harm associated with e-cigarette use [10,16,17]. The recognition of this association holds significant implications for public health, emphasizing the need for awareness campaigns and regulatory measures to mitigate the adverse effects on oral health. Moreover, the study acknowledges the diverse landscape of e-cigarettes in the United States, encompassing various brands and flavors, each containing distinct chemical compositions. Given this complexity, it is acknowledged that the study does not comprehensively analyze all individual chemicals present in different e-cigarettes. This limitation prompts a call for future experiments to undertake a more nuanced examination of the diverse chemical profiles within e-cigarettes to better understand their distinct impacts on oral mucosal tissues.

Despite the valuable insights provided by this study, certain limitations should be acknowledged. The decision to exclude factors such as alcohol consumption and daily routines may have implications for the generalizability of the findings. In addition, the complexity of e-cigarette compositions poses a challenge, as the study did not extensively investigate the myriad chemicals present in different e-cigarette products. Future research endeavors should consider a more comprehensive approach, encompassing a broader range of variables and a detailed analysis of the chemical constituents of various e-cigarettes.

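### The study is labelled case-control but selects both groups by e-cigarette use, and its temporality, causation and cancer claims go beyond the data collection it describes.

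*Protocol article*

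**What the plan says.** The Study Design section of the Protocol article states: "The adoption of a case-control, prospective, observational study design is motivated by the relatively low incidence of oral mucosal lesions within the general population". The section explains that a case-control study compares people who have the outcome with people who do not. It also says that participants will be tracked over time, "providing a temporal sequence crucial for establishing causation", and it describes the sampling as "focusing on a population at risk (e-cigarette smokers) and carefully selecting controls".

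Selection of the e-Cigarette Case Group admits people who used e-cigarettes over the last 210 days. Selection of Controls admits people with no history of e-cigarettes, alcohol or tobacco. Sampling Methods sets 152 users and 152 non-users, with planned proportions of 11% and 2.5%.

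Data Collection: Questionnaire describes an interviewer-administered questionnaire. One item is whether white spots are present. A life grid is used "to efficiently collect retrospective information on lifestyle habits and other risk factors".

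On what the study will show, Background says "this study will be the first to determine whether e-cigarettes are mechanistically linked to the development of oral cancer". Research Significance says the results may instead "exclude them as a cause of oral carcinogenesis". Discussion opens a paragraph with "The findings of this study align with existing literature on e-cigarettes", although Results states that no data have been collected.

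**The concern.** The design label fixes who is eligible, what is estimated and what may be concluded. Here the label and the described conduct disagree in three ways.

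- **Sampling.** Rare-outcome efficiency comes from enrolling people because they have the outcome. Enrolling by exposure does not give it.
- **Temporality.** If white spots are recorded as present, and people who already have them are admitted, a white spot that came before the first e-cigarette is counted as an effect of e-cigarettes.
- **Scope.** The measured outcome is white spots. A result in either direction says nothing direct about oral cancer or mechanism.

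At stake is an association between vaping and white spots being presented as causal if positive, or as clearing e-cigarettes of a role in cancer if null.

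**Working it through.** **1. What the planned proportions refer to.** By construction, e-cigarette exposure is 100% in one group and 0% in the other, so 11% and 2.5% cannot be exposure proportions. They must be lesion proportions within exposure groups. The Abstract agrees: it compares the odds of lesions between the two groups.

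**2. The plan's own figure on that reading.** Inputs from Sampling Methods: p1 = 0.11, p2 = 0.025, n = 152 per group, power 80%, significance level .04. Data Analysis uses .05. The text with the sample-size figures gives no sidedness, so two-sided is my assumption.

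Power = Φ{[d√n − z·√(2·p̄·(1−p̄))] / √(p1(1−p1) + p2(1−p2))}, with d = 0.085 and p̄ = 0.0675.

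At two-sided .04, z = 2.054: (0.085 × √152 − 2.054 × 0.3548) / 0.3497 = 0.913, so power is 81.9%. Fisher's exact test by enumeration gives 78.9% at .04 and 81.5% at .05. All are within 2 points of 80%. The 152 per group is therefore a sample size for comparing lesion proportions between exposed and unexposed people, not for case-control sampling.

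**3. Expected lesions.**
- Users: 152 × 0.11 = 16.7
- Non-users: 152 × 0.025 = 3.8
- Total: 20.5 of 304
- Members of the case group without a lesion: 1 − 0.11 = 89%

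**4. What case-control sampling would have looked like (illustration).** The implied odds ratio is (0.11/0.89)/(0.025/0.975) = 4.82. The document gives no exposure prevalence among lesion-free people, so p0 is assumed over a range. Exposure among those with lesions is p1 = 4.82·p0/(1 − p0 + 4.82·p0). With the pooled two-proportion formula, two-sided .05 and 80% power:

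| Assumed p0 | p1 | n per group |
|---|---|---|
| 5% | 20.2% | 74 |
| 10% | 34.9% | 43 |
| 20% | 54.6% | 30 |
| 30% | 67.4% | 27 |
| 50% | 82.8% | 32 |

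That is the kind of gain the rationale appeals to. The described sampling does not obtain it.

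**5. Tracking against data collection.** Study Design promises real-time exposure data and observation of lesions as they develop. The questionnaire section describes past habits taken by life grid, white spots recorded as present or not, and controls interviewed after cases. The general and group-specific eligibility criteria exclude no one for existing white spots. Data Analysis describes no analysis over time, yet says the group comparison will verify whether e-cigarettes cause harm.

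**6. What a null result would show (illustration).** Take 4/152 in each group.
- Odds ratio 1.0: SE of log OR = √(2/4 + 2/148) = 0.717; 95% CI 0.25 to 4.07.
- Prevalence ratio 1.0: SE of log PR = √(2/4 − 2/152) = 0.698; upper limit exp(1.96 × 0.698) = 3.93.

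Even for white spots, such a null leaves room for large effects. For cancer the study has no observations at all.

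**The case against.** **The prospective label.** A reader might infer that this is a single retrospective interview and hence plainly a cross-sectional study. The article does not say so. No section states that there is only one interview, and Study Design expresses an intention to follow participants. A visit schedule is detail that an article may leave to a fuller protocol. The word retrospective is attached to habits and risk factors; white spots are recorded as currently present. This part of the objection stands. What remains is that the tracking statement and the questionnaire section do not fit together and must be reconciled.

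**Hedging elsewhere.** The Objective speaks of association, Research Significance of preliminary evidence, and Background leaves the cancer question to later experiments. That is fair, but the unhedged sentences stand beside the hedged ones, so the document contradicts itself. That a null result would in fact be published as exoneration is a prediction and is not claimed here.

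**The size of a null result.** It is tempting to say that a fourfold increase could not be excluded. For the 4/152 example this holds for the odds ratio (upper limit 4.07) but not for the prevalence ratio (3.93).

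**No planned number changes.** True: the sample size reproduces, and the chi-square test and logistic odds ratio stay usable. The label and conclusions still need correcting.

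**Conclusion.** The concern holds in this form. The case-control label contradicts the section's own definition, and the rare-outcome rationale falls with it. This rests on the selection criteria alone, and a follow-up schedule in a fuller protocol would not change it.

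The temporal-sequence claim is not supported by the data collection shown. How many white spots predate vaping cannot be estimated from the document; each one among users adds 1/152 = 0.66 percentage points to a planned difference of 8.5 points.

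The mechanistic-link and cancer-exclusion claims are unsupported because only white spots are measured. The Discussion's findings are a drafting error, since no data exist. A flat verdict that the study is cross-sectional goes further than the text allows.

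**What to change.** 1. Delete the case-control label and the rare-outcome rationale. Call the groups exposed and unexposed. Report the prevalence difference and prevalence ratio beside the odds ratio (on the planning values: 8.5 points, 0.11/0.025 = 4.4, and 4.82).
2. Reconcile Study Design with Data Collection: Questionnaire in one of two ways:
   - describe a cross-sectional comparison by exposure and delete the temporal-sequence and causation wording; or
   - if follow-up is truly planned, state that white spots are recorded at entry and analyse only new lesions among people free of them at entry.
3. Limit conclusions to association with white spots. Delete the cancer-exclusion and mechanistic-link claims, and make the Discussion conditional on results.

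One tempting repair should not be adopted: a sensitivity analysis that drops lesions predating first e-cigarette use. Controls have no first-use date, so it removes events from the exposed group only and pushes the estimate towards or below the null.

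Cost: rewording and two extra summary measures, before anyone is recruited, at the price of weaker headline claims. The follow-up route keeps the prospective aim but costs more. It needs an entry assessment and later visits, and a check that 11% and 2.5% are plausible as proportions with new lesions.
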